### Blinding

Given the nature of the intervention itself, participants cannot be blinded. However, strategies will be in place to attain the highest level of blinding possible. The researcher making the visit to the intervention group to explain the app will be different from the nurse responsible for taking the measurements and the person in charge of carrying out brief counseling after the baseline evaluation visit. In addition, the researcher responsible for the statistical analysis will not know the group to which the participants belong. To prevent contamination between groups, no additional counseling or reinforcement will be made during the 3-month evaluation visit. In addition, the app will not be available for download until the study is completed.

### Analysis plan

#### General analysis

Results will be expressed by means and standard deviations for quantitative variables, or by frequency distributions and percentages in the case of qualitative ones. The normality of variables will be tested by means of the Kolmogorov-Smirnov test. When a normal distribution cannot be assumed, we will use the corresponding nonparametric tests. The chi-square test or Fisher’s exact test will be applied to analyze the association between independent qualitative variables. Using the Student’s t-test or the Mann-Whitney U test, the means between the two groups will be compared. The relationship between quantitative variables will be analyzed with the Pearson or Spearman correlation coefficients.

Analysis of the results for the main variable and the secondary variables will be carried out by intention-to-treat. In addition, app adherence will be the subject of a secondary analysis, as described in the results of the EVIDENT II study [66] (< 60 days and > 60 days), and other relevant subgroups will also be analyzed in terms of their physical activity or previous adherence to the Mediterranean diet.

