### Analysis of the effect of the intervention on primary (steps/day) and secondary outcomes

To analyze the changes at 3 and 6 months’ post-baseline in the primary (physical activity - steps/day) and the secondary outcome within the same group, the Student’s t-test or the Wilcoxon test will be used for paired data. The McNemar test will be used for dichotomous variables.

The intervention effect will be analyzed by comparing the changes between IG and CG in blood pressure and secondary variables by using ANCOVA and adjusting for possible confounders. The intervention effect over the period studied will be measured by a repeated measures analysis.

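### A normality pre-test may choose the between-arm test, and so the estimand, for steps/day, because its relation to the ANCOVA is not stated

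*Protocol article*

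**What the plan says.** Protocol article, General analysis: "The normality of variables will be tested by means of the Kolmogorov-Smirnov test". The next sentence is the switching rule: "When a normal distribution cannot be assumed, we will use the corresponding nonparametric tests". No significance level is given, nor whether raw values, changes or residuals are tested. The two-group comparison follows: "Using the Student’s t-test or the Mann-Whitney U test, the means between the two groups will be compared".

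The section on the effect of the intervention on primary and secondary outcomes uses the same fork for change from baseline, with steps/day named: "within the same group, the Student’s t-test or the Wilcoxon test will be used for paired data".

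For the effect between arms, that section prescribes "comparing the changes between IG and CG in blood pressure and secondary variables by using ANCOVA and adjusting for possible confounders", and adds: "The intervention effect over the period studied will be measured by a repeated measures analysis". Neither sentence has a normality condition or a rank alternative.

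The sample size section bases the trial on a difference of 1850 steps/day with SD 3847, two-sided alpha 0.05, power 0.80, 80 per group and 15% dropout. The primary outcome is the change in steps/day by accelerometer.

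**The concern.** A Mann-Whitney test does not compare means. It yields no difference in mean steps/day and cannot adjust for baseline. If the pre-test governs the primary comparison, the trial answers one of two questions, and the observed data decide which. The reader could then be left without an estimate on the scale used for the sample size.

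The text does not exclude this. The ANCOVA sentence names blood pressure, which is not an outcome of this trial, where steps/day would be expected. Taken literally, the only named two-group test that covers steps/day is the gated t-test or Mann-Whitney pair. If ANCOVA is meant for steps/day, the general rule asks for a corresponding nonparametric test, and none is named. The subgroup section repeats the same analyses, so a subgroup and the whole trial could also be sent to different tests.

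**Working it through.** **1. The plan's own figure.** n per group = 2 × (1.960 + 0.842)² × 3847² / 1850² = 2 × 7.849 × 4.324 = 67.9, so 68. With 15% dropout, 68 / 0.85 = 80. The stated size is reproduced, and it is sized on a difference in means.

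**2. Where the gate applies.**

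| Analysis | Subject to the gate? | Covers steps/day? |
|---|---|---|
| t-test or Mann-Whitney, two groups | yes | yes, as a general rule |
| Paired t-test or Wilcoxon, within group | yes, by the same fork | yes, by name |
| ANCOVA, between arms | not stated | not named |
| Repeated measures | not stated | not specified |

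The within-group row does not determine the treatment effect. The open question lies between the first and third rows.

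**3. How the gate would act.** The protocol gives no distribution or correlation, so the following are assumptions: 68 completers per arm, true effect 1850, and Kolmogorov-Smirnov with Lilliefors p-values at 0.05 applied to the change from baseline.

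*Model A.* SD of the change is 3847. Baseline and residual terms are normal or gamma-type with skewness 1 or 2. The baseline to 3-month correlation is r. There are 1500 runs per row. The columns from ANCOVA to K-S, then Mann-Whitney else ANCOVA show power.

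| Shape, r | K-S rejects | ANCOVA | t on change | Mann-Whitney on change | K-S, then t or Mann-Whitney | K-S, then Mann-Whitney else ANCOVA | t and Mann-Whitney disagree |
|---|---|---|---|---|---|---|---|
| normal, 0.5 | 3.2% | 0.888 | 0.795 | 0.774 | 0.795 | 0.887 | 5.0% |
| normal, 0.7 | 3.0% | 0.855 | 0.801 | 0.786 | 0.804 | 0.855 | 6.1% |
| skewness 1, 0.5 | 26.2% | 0.894 | 0.803 | 0.820 | 0.811 | 0.879 | 6.0% |
| skewness 1, 0.7 | 42.3% | 0.848 | 0.779 | 0.823 | 0.803 | 0.841 | 8.0% |
| skewness 2, 0.5 | 84.4% | 0.894 | 0.791 | 0.925 | 0.912 | 0.929 | 13.9% |
| skewness 2, 0.7 | 95.1% | 0.859 | 0.790 | 0.935 | 0.933 | 0.937 | 14.7% |

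With no true effect, the type I error of K-S then t or Mann-Whitney was 0.037 to 0.052. That of ANCOVA with a switch to Mann-Whitney was 0.042 to 0.051.

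Power change from adding the switch to ANCOVA:
- Skewness 1: 0.879 − 0.894 = −0.015 and 0.841 − 0.848 = −0.007.
- Skewness 2: 0.929 − 0.894 = +0.035 and 0.937 − 0.859 = +0.078.

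*Model B.* Steps at each visit are gamma-distributed with mean 7000 and SD 3847, and r = 0.5, 0.6 or 0.7 (2000 runs each). The SD of the change is then about 3847 × √(2 × (1 − r)), for example 3441 at r = 0.6, so power rises with r. K-S rejects normality of the change in about 14 to 16% of trials.
- ANCOVA power: 0.885, 0.915, 0.968.
- ANCOVA with the switch: 0.875, 0.913, 0.968, a loss of 0.010, 0.002 and 0.
- K-S then t or Mann-Whitney on change: about 0.79 to 0.94 across the same range.

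**4. The undefined gate.** Under Model B with r = 0.6, Lilliefors rejects normality of the change in 16% of trials and uncorrected K-S in 0.5%. For raw 3-month values the figures are 78% and 17%. All four are compatible with the text.

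**The case against.** The strongest reply is that the gate never touches the treatment effect. The pairs of tests stand under a general heading. The section on the intervention effect prescribes ANCOVA and a repeated measures analysis without conditions. ANCOVA has no standard rank counterpart, so there may be nothing corresponding to switch to. On that reading ANCOVA stands whatever K-S shows. The statistician is also blinded to group, which limits exploitation of the choice, and an article may leave covariates and residual checks to a fuller plan.

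Much of this stands. A reader might infer that a failed normality test removes the baseline-adjusted estimate. The documents do not say so. It follows only if the general rule overrides the later section, and the protocol never names baseline steps/day as a covariate in the first place.

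A reader might also infer that the switch inflates type I error or must lose power. Neither is supported. A marked loss appears only if raw 3-month values are tested and baseline is discarded, whereas the stated outcome is the change.

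What does not stand is that this is merely omitted detail. The switching rule is written down, it is general, it describes Mann-Whitney wrongly, and the one sentence that could exempt the primary outcome does not name it.

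**Conclusion.** The point holds in a limited form. The protocol does not fix one between-arm analysis for steps/day, and a pre-test with no stated level, variant or target may choose it. The consequence is an estimand that can move away from the mean difference on which the trial was sized. When the effect is real, the t-test and Mann-Whitney gave different significance verdicts in about 5 to 15% of simulated trials, so the branch can matter.

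Type I error is not materially affected. The power effect of switching away from ANCOVA depends on the distribution: about 1 point or less in Model B, 0.7 to 1.5 points lost at skewness 1 in Model A, and about 4 to 8 points gained at skewness 2. ANCOVA exceeds the gated t-test or Mann-Whitney pair in Model B (about 0.89 to 0.96 against 0.79 to 0.94) but not under the heavier skew. The case for ANCOVA therefore rests mainly on the fixed estimand. Mean, shape, correlation and K-S level are all assumptions.

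The mention of blood pressure is a separate defect. It matters here because it leaves the question open.

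**What to change.** - State that the between-arm effect on steps/day is estimated by ANCOVA of 3-month steps/day (or its change) on group and baseline steps/day. Report it as an adjusted mean difference with a 95% confidence interval, regardless of any normality test. Use a robust or bootstrap interval if residuals are skewed.
- Remove the Kolmogorov-Smirnov gate for outcome comparisons.
- Keep Mann-Whitney or a rank-based ANCOVA only as a sensitivity analysis named in advance.
- Correct the sentence saying that Mann-Whitney compares means.

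The cost is wording. The sample size and data collection do not change. If the change in steps/day is heavily skewed, some power may be given up against a rank test: at skewness 2 in Model A, 0.894 against 0.925 (r = 0.5) and 0.859 against 0.935 (r = 0.7). ANCOVA still stays above the planned 0.80 there.

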### Sample size calculation

The sample size was estimated for the main variable of the study (Physical activity - steps/day). Assuming a standard deviation of 3847 steps/day [49], a power of 0.8 and an alpha risk of 0.05 in a bilateral test, 80 participants are necessary in each group to detect an increase of 1850 steps/day in the experimental group compared to the control group. This calculation was based on the estimate by Alonso-Dominguez et al. [50]. We assumed a dropout rate of 15% throughout the duration of the study (3 months).

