### Intervention

Common to both groups: before randomization, all participants (control and intervention), will receive nutritional counseling aimed at good compliance with the Mediterranean diet. Counseling will consist of a 10-min individual appointment in which the ideas behind the Mediterranean diet will be outlined, as well as the health benefits and evidence generated by this pattern of nutrition. Both groups will also receive brief counseling on physical activity aimed at complying with the current recommendations for both the general and the elderly population, and will be advised to perform at least 30 min of moderate activity for five days a week, or 20 min of vigorous activity three days a week. Participants will be provided with an informative leaflet at the end of the session.

Specific intervention in the experimental group: Participants in the intervention group will be issued with a smartphone (Samsung Galaxy J3) and a smartband (Xiaomi Miband S2) for the duration of intervention (3 months). During an approximately 15-min visit, each participant will be trained to use the device and the app developed for the EVIDENT 3 study [52] (Intellectual Property Registry No. 00/2017/2438), which is pre-installed on the smartphone. In the first part of this visit, the app will be configured with a series of data (age, sex, weight and height) which will allow the daily energy needs of each participant to be calculated. The app allows daily monitoring of food and physical activity by integrating the information collected by the smartband regarding physical activity (steps, calories and heart rate) and information related to food after the subject has logged food or dishes eaten each day, selected from the app menu –Fig. 2. At the end of the day, the application makes recommendations and a personalized plan to improve eating habits and physical activity over the following days. At the 3-month visit, the devices will be taken back.

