#### Other variables

Motivation for change, as described by Prochaska and Diclemente, will be assessed at baseline, classified into the different stages of pre-contemplation, contemplation, determination, action, maintenance and relapse. With intervention group participants, app adherence will be measured by the number of logs and days on the device.

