### Analysis by subgroups

The intervention effect could be affected by age, sex, educational level and adherence to the application during the study, as well as motivation and lifestyles at the baseline assessment. The same analyses described above will be performed for each of the aforementioned subgroups.

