### Secondary analyses

Multiple multivariate regression analysis will be performed to identify the variables with the greatest influence on physical activity changes and the secondary variables analyzed.

All analyses will be carried out with SPSS version 23.0 (IBM Corporation, Armonk, NY, USA) and an alpha risk of 0.05 will be assumed as the limit for statistical significance.

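### The secondary app-adherence analysis is specified only as a single cut at 60 days, although days of use are counted; if that cut is the only analysis it loses material power, and exactly 60 days is left unassigned

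*Protocol article*

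**What the plan says.** Under Other variables, the Protocol article states for intervention-group participants that "app adherence will be measured by the number of logs and days on the device". Both are counts. Under General analysis it states that "app adherence will be the subject of a secondary analysis, as described in the results of the EVIDENT II study", and gives the classes as "< 60 days and > 60 days". No other form of the adherence analysis is named, and no rule is given for a participant with exactly 60 days.

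Three other statements bear on the point:

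- Analysis by subgroups lists "age, sex, educational level and adherence to the application during the study" among the factors that could affect the intervention effect, and plans to repeat the main analyses in each subgroup.
- General analysis also says: "The relationship between quantitative variables will be analyzed with the Pearson or Spearman correlation coefficients".
- Secondary analyses says: "Multiple multivariate regression analysis will be performed to identify the variables with the greatest influence on physical activity changes".

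Neither of the last two names adherence. The main and secondary outcomes are to be analyzed by intention-to-treat.

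**The concern.** An adherence analysis of this kind asks whether more use of the app goes with more benefit. A single cut treats a participant with 59 days as equal to one with 0 days, and one with 61 days as equal to one with 90. If outcome rises fairly steadily with use, that discards information the trial has already collected, in an analysis that can draw on one arm only. A real gradient could be missed and reported as no association.

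The second matter is smaller. Sixty days is an attainable value in a 3-month device period, and the two inequalities as printed do not cover it. Unless the boundary is settled elsewhere, someone would have to place such a participant once adherence data exist.

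**Working it through.** **1. Number of participants.** The article assumes an SD of 3847 steps/day, a difference of 1850 steps/day, power 0.80, two-sided alpha 0.05 and 15% dropout (Sample size calculation).

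- n per arm = 2 × (1.960 + 0.842)² × 3847² / 1850² = 67.9, rounded up to 68.
- With dropout: 68 / 0.85 = 80, the stated figure.

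The sample size reproduces and is not at issue. It gives about 68 intervention completers for the adherence analysis. The article states no power for that analysis.

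**2. Participants at exactly 60 days.** The article gives no distribution of days, so this is an assumption. With use uniform over 0 to 90 days (91 values):

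- expected number = 68 / 91 = 0.75
- chance of at least one = 1 − (90/91)^68 = 0.53

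Other broad assumed shapes (skewed high, U-shaped, skewed low) give 0.45 to 1.25 expected among 68. Only a shape tightly clustered around 60 gives more, 3.4 of 68. Leaving these participants out costs at most about 2 points of power: 0.602 against 0.625 in the clustered case, and less than 1 point in the others.

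**3. Power with days as a count and after the cut.** Assumptions: a roughly linear relation with correlation r between days of use and change in outcome, n = 68, two-sided alpha 0.05. By Fisher's z:

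- power = Φ(atanh(r) × √(n − 3) − 1.96), with √65 = 8.062.
- After a split, r becomes r × c, where c is the correlation between days and the two-class indicator. For a normal variable with a proportion q on one side, c = φ(z_q) / √(q(1 − q)).
- For q = 0.5, c = 0.798, so the split keeps c² = 0.64 of the information. For q = 0.8, c = 0.700 and c² = 0.49.

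| r | Days as a count | Split 50/50 | Split 80/20 |
|---|---|---|---|
| 0.3 | Φ(2.495 − 1.96) = 0.70 | Φ(1.968 − 1.96) = 0.50 | Φ(1.718 − 1.96) = 0.40 |
| 0.4 | Φ(3.416 − 1.96) = 0.93 | Φ(2.666 − 1.96) = 0.76 | Φ(2.319 − 1.96) = 0.64 |

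**4. Same question from a fixed starting point.** A correlation detectable with 80% power as a count at n = 68 is r = tanh(2.802 / 8.062) = 0.33. Under the assumed shapes in which 33% to 68% of participants exceed 60 days, and for a normal split at the median, the cut keeps 64% to 76% of the information and power falls to about 60% to 68%. With splits as uneven as 80/20 to 93/7 it keeps 33% to 49%, and power falls to about 35% to 49%.

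Nearly all the loss therefore comes from cutting the count in two. The unassigned value at 60 contributes little.

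**The case against.** The strongest case on the other side has five parts.

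- **The cut is not shown to be the only analysis.** The article keeps days and logs as counts and plans correlations between quantitative variables and a multiple regression. This stands in part: those sentences leave room for days as a count. They do not plan it, since neither names adherence and the regression lists no covariates. The power loss must therefore be stated conditionally.
- **The cut comes from an earlier study in the same programme.** Comparability is a fair reason to keep the two classes. It is no reason to omit the count. The boundary at 60 may also be settled in that study or in the full plan, neither of which is shown.
- **The figures rest on assumptions.** This stands. The correlations, the distribution of days and the linear relation are not in the article. If benefit appears only beyond a threshold near 60 days, the cut could lose little or nothing.
- **The analysis modelled is one of several possible.** The subgroup section could mean a comparison of adherence classes with the control group. The calculation here covers only a within-arm analysis, and the article does not say how the classes would enter.
- **Adherence is observed after randomization and only in one arm.** This stands for either form of the analysis. Neither gives a randomized comparison.

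A reader might infer that participants with 60 days will be dropped. The article contains no exclusion rule; the wording looks like a missing equals sign. A reader might also infer that power has definitely been lost or that the trial's main result is weakened. Neither follows: the loss depends on the cut being the only adherence analysis, and the primary comparison does not use adherence.

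**Conclusion.** The point holds as a cheap improvement. The article names one form for its adherence analysis, a single cut at 60 days, although it records a count. If nothing else is done with adherence, and if the relation is roughly linear with r of 0.3 to 0.4 in about 68 participants, power is about 70% to 93% with days as a count and about 50% to 76% after a near-balanced split. For an 80/20 split it is about 40% to 64%. The gap at exactly 60 days is a wording matter, likely to concern 0 to 2 participants under broad assumed distributions. The stated sample size, the primary outcome and its intention-to-treat analysis are untouched.

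**What to change.** In the General analysis section:

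1. Make the classes exhaustive, for example < 60 and ≥ 60 days, or use the earlier study's own boundary, fixed before adherence is related to outcome.
2. Prespecify days of use as a continuous variable (for example per 10 days) as the main adherence analysis within the intervention arm.
3. Keep the two-class result for comparison with the earlier study.
4. Label both as non-randomized associations with a post-randomization variable.

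The cost is one symbol and a sentence or two; days of use are already to be recorded. The downside is that the continuous analysis assumes an approximately linear relation, which should be checked, for instance with a plot of outcome change against days.

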### Analysis of the effect of the intervention on primary (steps/day) and secondary outcomes

To analyze the changes at 3 and 6 months’ post-baseline in the primary (physical activity - steps/day) and the secondary outcome within the same group, the Student’s t-test or the Wilcoxon test will be used for paired data. The McNemar test will be used for dichotomous variables.

The intervention effect will be analyzed by comparing the changes between IG and CG in blood pressure and secondary variables by using ANCOVA and adjusting for possible confounders. The intervention effect over the period studied will be measured by a repeated measures analysis.

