### Hypothesis and objective

The main hypothesis of the EVIDENT-Age study is that lifestyle improvements among the over-65 population, achieved through the combined use of smartphones and smartbands, could have an influence in terms of improving body composition, quality of life, daily living activities and cognitive performance.

The objective of this study is to assess the effectiveness of the combined use of smartphone and smartband technology for 3 months alongside brief counseling on life habits, versus counseling alone, in increasing physical activity and improving adherence to the Mediterranean diet. As a secondary objective, we will assess the effect of the intervention on body composition, quality of life, daily living activities and cognitive performance.

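### The between-arm ANCOVA names blood pressure instead of steps/day, so the only test in that section tied by name to the primary outcome is a paired test inside each arm

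*Protocol article*

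**What the plan says.** All references are to the Protocol article.

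- **Objective (Hypothesis and objective).** The question is a contrast between arms: smartphone and smartband technology "alongside brief counseling on life habits, versus counseling alone, in increasing physical activity" and in improving diet.
- **Common treatment (Intervention).** "Both groups will also receive brief counseling on physical activity aimed at complying with the current recommendations".
- **Analysis of the effect of the intervention, first paragraph.** For changes from baseline in steps/day and the secondary outcomes, "within the same group, the Student’s t-test or the Wilcoxon test will be used for paired data". McNemar's test is added for dichotomous variables.
- **Same section, second paragraph.** The intervention effect is to be examined by comparing changes between the two groups with ANCOVA, adjusted for confounders. The variables listed are blood pressure and the secondary variables. A repeated measures analysis follows, with no outcome named.
- **Analysis by subgroups.** The same analyses are repeated by age, sex, education, app adherence, motivation and baseline lifestyle.
- **Secondary analyses.** For all analyses, "an alpha risk of 0.05 will be assumed as the limit for statistical significance".
- **Sample size calculation.** The trial is sized to "detect an increase of 1850 steps/day in the experimental group compared to the control group".

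**The concern.** Each arm's change from baseline contains everything the two arms share: the counseling, the effect of being observed, season and regression to the mean. Randomization removes these only when the arms are compared with each other. A significant rise in the intervention arm is therefore not evidence for the app. A rise that is significant in one arm and not in the other is not a test of the difference between them, and its error rate is not held at 0.05.

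This would matter little if the between-arm test of steps/day were plainly specified beside the paired tests. It is not. Blood pressure appears neither in Table 1 (Timeline of measures) nor among the primary and secondary outcomes, and it stands where the primary outcome should be. Read literally, the section gives steps/day a within-arm test by name and a between-arm test only by inference.

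The subgroup plan widens the gap. App adherence is recorded only in the intervention group (Other variables). A subgroup defined by it has no control participants, so of the listed tests of change the paired test is the one that can be run as written.

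**Working it through.** **1. Which test is tied to steps/day.**
- Paired t or Wilcoxon, within arm: named for the primary outcome.
- ANCOVA of change, between arms: named for blood pressure and secondary variables.
- Repeated measures: no outcome named.
- Two-group t-test or Mann-Whitney (General analysis): generic, no outcome named.

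**2. Reproducing the plan's sample size.** Inputs from Sample size calculation: SD 3847, difference 1850, two-sided 0.05, power 0.80, dropout 15%.
- n per arm = 2 × (1.96 + 0.842)² × 3847² / 1850² = 67.9, so 68.
- 68 / (1 − 0.15) = 80, which agrees with "80 participants are necessary in each group".
- Power with 68 completers per arm is 80.1%. The stated size thus already powers the between-arm contrast.

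**3. How often would only the intervention arm show a significant rise if the app did nothing?** The documents give neither the rise common to both arms nor the SD of change. Both are assumed here: rises from 0 to 1850 steps/day, and an SD of change equal to the planning SD of 3847.
- Standard error of an arm's mean change = 3847 / √68 = 466.5.
- Noncentrality = common rise / 466.5, for a paired t-test on 67 degrees of freedom at two-sided 0.05.
- Let p be the probability that an arm's test is significant, and u the probability that it is significant in the upward direction.
- P(only the intervention arm significantly up) = u × (1 − p), because the arms are independent.

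| Common rise (steps/day) | u | p | u × (1 − p) |
|---|---|---|---|
| 0 | 0.025 | 0.050 | 2.4% |
| 500 | 0.183 | 0.184 | 15% |
| 750 | 0.354 | 0.354 | 23% |
| 1000 | 0.561 | 0.561 | 25% |
| 1500 | 0.887 | 0.887 | 10% |
| 1850 | 0.974 | 0.974 | 2.5% |

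The maximum is 25%, reached where p is near one half (a rise of about 914). With all 80 per arm analysed, rises of 500, 750 and 1000 give 17%, 24% and 23%.

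**4. Sensitivity to the SD.** If 3847 is a cross-sectional SD and the baseline to follow-up correlation is 0.7 to 0.8 (assumed), the SD of change is 3847 × √(2 × (1 − r)) = 2980 to 2433. The maximum stays near 25% but moves to a smaller common rise, about 750 (r = 0.7) to 500 (r = 0.8) steps/day.

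**5. The between-arm test under the same conditions.** In 20,000 simulated trials at each common rise of 500, 914 and 1000, with no app effect, a two-sample t-test of change was significant in 5.3%, 4.8% and 4.7%. That is about 5% two-sided, or about 2.5% in favour of the app.

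**The case against.** The best defence is the paragraph that follows the quoted one. There the term intervention effect is attached only to between-arm ANCOVA and repeated measures, while the paired tests have the separate stated purpose of describing change inside a group. The objective and the sample size are between-arm, the section heading names steps/day, and blood pressure looks like a slip. Paired tests beside a between-arm analysis are an addition, and labelling them is often left to a fuller document.

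Much of this stands. A reader might infer that the plan judges the app by within-arm p-values, that nothing assigns the intervention effect to any test, or that the trial's false-positive rate is 15% to 25%. The documents support none of these. No section adopts the rule of significance in one arm and not the other, so the percentages describe a possible misreading and not the error rate of the plan. They also fall to about 2.5% at both ends of the range.

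What does not stand is that this is labelling alone. The ANCOVA sentence lists the wrong variable, and that is an error in the text, not a detail left out. It removes the primary outcome from the one sentence that should fix its between-arm test. The adherence subgroups then leave a within-arm p-value with no control comparison beside it.

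**Conclusion.** The concern holds in a limited form. The plan intends a between-arm analysis of the intervention effect but, through the blood pressure wording, does not name steps/day in it. Within-arm tests at 0.05 are the only ones in that section explicitly assigned to the primary outcome, and since both arms are counseled they do not estimate the app effect. If a rise significant only in the intervention arm were taken as an effect, the pattern would arise with no app effect in about 2% to 25% of trials, against about 2.5% in that direction for the between-arm test. The range rests on an assumed common rise of 0 to 1850 steps/day, an assumed SD of change of 3847 and 68 completers per arm. The risk is greatest at intermediate rises. The point should be corrected, but it does not invalidate the design or the sample size.

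**What to change.** In the section on analysing the effect of the intervention:

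1. In the ANCOVA sentence, replace blood pressure with 3-month change in steps/day and identify it as the primary outcome. Three months is the only follow-up point at which Table 1 schedules the accelerometer.
2. Add a sentence such as: *Conclusions about the intervention rest only on the between-arm comparison of change, IG versus CG; for the primary outcome this is the 3-month change in steps/day.*
3. Replace the paired t, Wilcoxon and McNemar tests with within-arm mean change, or change in proportion, with 95% CI and no p-value. Apply the same to Analysis by subgroups, including the app-adherence groups.

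The cost is a few sentences and fewer tests. No extra participants, visits or data are needed, and the 80 per group is unchanged.
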